
### Outcomes {12}

#### Implementation process outcomes (Aim 1).

We will conduct multimethod qualitative research to document all implementation strategies done, to assess modifications to the implementation of GlobalConsent and to implementation plans, and to understand barriers/facilitators to implementation across HIS and LIS groups (Table 4). Twelve group reflections between CCIHP and the study team will be conducted to understand the GlobalConsent implementation process and modifications to the implementation plan in the LIS and HIS groups. Two key informant interviews (KIIs [46]) with each of 30 university leaders (five [56] leaders per university; 15 leaders per IS group; 60 KIIs total) will collect in-depth data from individuals who are knowledgeable about external factors (policies, regulations, funding) and organizational factors (resources, time constraints, institutional climate, leadership support) that may explain modifications to GlobalConsent and implementation plans [46]. A semi-structured interview guide, with open-ended questions and prompts, will guide the KIIs (**Appendix**). Focal topics before implementation will include 1) perceptions about sexual violence among university students and 2) perceptions about the feasibility, acceptability, and suitability of sexual violence prevention programs at universities. Focal topics after implementation will include these topics as well as 1) attitudes of university leaders, faculty, and students about continued implementation of GlobalConsent, 2) barriers and facilitators of future implementations with detailed probes, and 3) external contextual factors that may affect future implementation.

Longitudinal focus group discussions (FGDs) will entail four discussions with each of six groups of 5–8 [57] implementation team members (one group per university; 24 FGDs total). These FGDs will provide detailed, near-real-time data on the project’s dynamic implementation context, including features of the implementation setting; modifications to GlobalConsent or implementation plans; changes in the university, local, regional, or national context that may affect implementation; and team sense-making and learning [58]. The FGD guide [46] includes open-ended questions aligned to FRAME; the rationale, timing, and guidance for each question; and probes about the use of core implementation strategies (**Appendix**). Some questions in the FGD guide are like those in the KII guide to facilitate triangulation of the data during analysis.

A brief checklist will be added at the end of every program module of GlobalConsent (**Appendix**). This checklist will be based on the Modifications and Adaptations Checklist [59, 60], a coding scheme for recording modifications to evidence-based interventions. The checklist will ask participants to self-report any modifications they made to planned use of GlobalConsent. As students cannot skip segments or modules in GlobalConsent, the checklist will focus on the following major modifications: 1) device used to view each module of GlobalConsent, 2) percentage of module watched, 3) number of sessions required to watch the module, 4) whether or not they watched part or all of each module mor than once; 5) ‘drift’ by multi-tasking or doing other things while a module was open, 6) ‘drift’ by stepping away from the computer or mobile device while a module was open, 7) extent of satisfaction with the content of the module, and 8) any comments about the module.

#### Implementation drivers and outcomes (Aim 2).

Table 5 summarizes the constructs to be measured, data sources, study samples, number of assessment points by focal population, and for variables measured in surveys (indicated with a superscript), the number of items per construct. The main constructs to be measured are drawn from implementation science and based on the hypothesized processes and outcomes in the present study. Scales that were created to assess general implementation of evidence-based practices in a medical or social-service setting are adapted to fit the current context of implementation by modifying item wording to focus generally on sexual violence prevention programming and specifically on GlobalConsent in a university context (**Appendix)**.

Demographic implementation drivers that are measured in all focal populations include age in years, sex assigned at birth, gender identity, sexual orientation, and ethnicity. Questions on sex, gender, and sexual orientation are based on recommendations from the National Academies of Sciences, Engineering, and Medicine (NASEM) [61]. Normative implementation drivers include pre-implementation perceptions in all focal populations about sexual violence as a problem to address, perceptions of campus climate, legal knowledge of sexual violence, knowledge about active consent, and rape-myth acceptance. Other implementation drivers include perceptions of implementation 1) leadership, 2) collaboration, and 3) climate.

Implementation outcomes include the 1) perceived acceptability, appropriateness, and feasibility of general sexual violence prevention programming in all focal populations, 2) perceived acceptability, appropriateness, and feasibility specifically of GlobalConsent in all focal populations, 3) implementation adoption among eligible students consenting to take part in GlobalConsent, and 4) implementation penetration among eligible students consenting to take part in GlobalConsent. Intervention adoption and penetration will be measured continuously using records from the collaborative IT company on the implementation of GlobalConsent by tracking the number of eligible male student participants who consent to take part in GlobalConsent (adoption) and who complete the intervention (penetration). Notably, the normative climate among leaders, faculty, and implementation teams at baseline also may change as a result of implementation, so these measures are listed as implementation outcomes.

#### Implementation effectiveness outcomes (Aim 3).

Student-level primary outcomes (sexually violent behavior; prosocial intervening behavior) and student-level secondary outcomes related to cognition/knowledge, attitudes/beliefs, affect, and capacity are summarized in Table 6, and all question sets are provided in English and Vietnamese in the **Appendix**. Table 6 also includes the National Institutes of Health (NIH) common data elements to be collected.

#### Incremental cost effectiveness outcomes (Aim 4).

The primary effectiveness outcomes for the cost-effectiveness analysis will be the frequency of sexually violent behavior and prosocial intervening behavior. The costing items are organized sequentially based on the implementation phases: pre-implementation, implementation, and post-implementation. Each phase includes a detailed list of activities (Tables 2, 3), with costs related to personnel, travel, space, and supplies/equipment collected for each activity. We will estimate the aggregate costs for each university and then divide this aggregate by the total number of participants at that university to determine the cost per participant.

### Participant timeline {13}

Figure 2 summarizes the start dates and end dates for enrolment (X), interventions (implementation activities and delivery of GlobalConsent), and assessments (X) with each focal population in the “high intensity” implementation strategies group.

### Sample size {14}

Focal populations for each of these assessments include university leaders who support the GlobalConsent implementation (n=5 per university, total of 30); members of implementation teams (n≈5 per University, total≈30 members); fulltime permanent faculty at each university (estimated mean 589 per university, range 186–1038, total 3,532; based on official figures for 2021), and male student participants in GlobalConsent (estimated mean n=796 per university, range 449–1202, total=4,776 18–24 year-old, first-year undergraduate, heterosexual or bisexual men, who are attracted to women; based on official enrolment figures for 2021). We will assume 80% participation and 90% retention in each focal population.

### Recruitment {15}

#### University leaders (Aim 1).

University leaders will be identified purposively via discussions between CCIHP key personnel and implementation team focal persons. Eligible participants will be informed during the online informed consent process that they will be compensated $10 for completing each of two online surveys and $20 for completing each key informant interview (KII), for a total compensation of $60 for completing all assessments.

#### Implementation team members (Aims 1, 2, and 4).

Implementation team supervisors and team members will be identified purposively via discussions between CCIHP key personnel and the identified focal implementation team member in each university and finally approved by the leaders of that university. Eligible implementation team members will be informed during the online informed consent process that they will be compensated $10 for completing each of four online surveys and $16 for participating in each focus group discussion (FGD), for a total compensation of $104 for completing all assessments.

#### University faculty (Aim 2).

Each university will submit to non-study staff the list of all permanent, fulltime faculty (lecturers) at their university, with professional contact details. All eligible lecturers will receive an email invitation from staff within the university introducing the study and inviting their participation. Two days later, each faculty member will receive a secure REDCap link to the informed consent form. While completing the online consent form, faculty will have an opportunity to call a non-study staff member to answer any questions about the study, as needed, before consent and participation. Faculty will be informed during the consent process that they will receive $10 for completing each online survey. If consent is confirmed, the faculty member will be directed immediately to the online REDCap survey. Any faculty member who has not completed the online survey will receive up to five automated reminders from REDCap at 2.5-day intervals over two weeks. In addition, on day 8 and 15 of the survey period, all faculty will receive a reminder invitation from within their university to complete the survey. On day 22 and 29 of the survey period, any faculty member who has not completed the survey will receive additional reminder invitations. During the two weeks following day 15, any faculty member who still has not completed the survey will receive up to two standard SMS text reminders with their unique survey link encouraging them to complete the survey. If, after four weeks, faculty have not yet completed the faculty survey, they will receive a standard follow-up reminder and unique survey links via Zalo and a call via Zalo, an encrypted Vietnamese communication application similar to Whatsapp. Once this protocol is completed, implementation teams will send a general reminder through informal faculty networks at their universities for faculty to complete the survey.

#### First-year undergraduate male students (Aims 1 and 3).

All eligible students will be invited to participate in 6 six-monthly surveys and the GlobalConsent program. For the LIS and HIS groups, implementation team members will send a standard email invitation to all eligible men with a description of the GlobalConsent program, a description of the study, and an invitation to participate. They will separately receive a secure REDCap link to the online informed consent form, and if completed, the online survey (Table 6). For the HIS group, internal facilitators will organize an orientation session for all eligible male students to describe these elements in person and to answer any questions about participation. All eligible participants will be informed during the online informed consent process that they will be compensated $5.50 in average for completing each survey assessment, for a total compensation of $33 for completing all six assessments. All eligible participants also will be informed during the online informed consent process that they will be eligible to enroll in a lottery to receive a prize (e.g., smartphone) after completing three survey assessments, and that they will be eligible to enroll in a second lottery to receive a prize (e.g., smartphone) after completing six survey assessments. All eligible participants in the HIS group will be informed about this compensation schedule during the recruitment orientation meeting.

## Assignment of interventions: allocation

### Sequence generation {16a}

All universities in the sample are broadly matched on programs of study (health sciences) and are pair-matched on region (North, Central, South). Within matched pairs, universities will be randomized using a computer random number generator to receive ‘lower intensity’ (LIS) or ‘higher intensity’ (HIS) implementation strategies to deliver GlobalConsent to eligible undergraduate men.

### Concealment mechanism {16b}

The team will separate the act of randomization from the recruitment of participants as follows. First, CCIHP will be responsible for completing the randomization of university to IS groups. Second, a staff member at each participating university will be responsible for recruitment strategies within their respective university. Third, Emory study staff will pre-program the REDCap data system to send automated reminders to participate in each study wave, at the schedules described previously.

### Implementation {16c}

Non-study staff at CCIHP will generate the allocation sequence, randomly assign universities to study arms, and upload contact lists for eligible participants in each focal population into REDCap. Formal invitations to participate will be sent automatically via the customized REDCap data system, or for university leaders, by the staff member at CCIHP conducting KIIs.

## Assignment of interventions: Blinding

### Who will be blinded {17a}

Implementation teams at each university will be blinded to the bundle of implementation strategies to which they are being compared. Students will be blinded to the implementation strategies being implemented at their and other universities, except for the strategies to which they are directly exposed. Study team members at Emory University and Georgia State University will be blinded to the assignments of universities until analyses are completed by using a non-ordered numerical assignment to university and study arm in the REDCap database. Members of the data safety and monitoring board will be blinded to implementation strategy assignments until they request to be unblinded.

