### Strategies to improve adherence to interventions {11c}

To improve implementation-team adherence to the LIS and HIS implementation strategies protocols, Emory and CCIHP will establish deliverable-based contracts with each university clarifying the terms of reference (TOR) and payment schedule for mutually agreed implementation activities. At the time of implementation team training, each team member at each participating university will assume specific roles and responsibilities, and a team supervisor will be responsible for overseeing the activities of all implementation team members. The completion of all activities will be assessed at the time that each university invoices CCIHP for its work, and payment of invoices will be based on the demonstrated completion of implementation activities in the TOR.

To support students’ adherence to the GlobalConsent program in the HIS group, the contracted IT company (with support from internal implementation team members) will send students weekly email and/or text reminders to complete each program module. In the LIS group, the contracted IT company, with support from internal implementation team members, will send students email and/or text reminders once every two weeks to complete each program module. Students will be offered to enter their unique ID into a lottery to win a small prize for completing each module. Student adherence to program participation will be monitored with a short survey after each program module and with passive monitoring by the IT company delivering the program (times module opened, time spent with module open).

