#### Quantitative data (Aim 1 Checklist, Aims 2–3).

The REDCap data system will be used to facilitate secure data collection, transfer, processing, and storage of quantitative data. Data-collection modules for each wave will be built in a REDCap project and self-administered on personal devices to ensure flexibility and privacy. All required fields (e.g., documentation of consent) are specified as such, and participants cannot continue with the survey until required responses are completed. Allowable response options for each question are programmed into the data system, and participants are asked to correct or to confirm any missing or out-of-range responses. Each page of the application includes a check at the bottom to ensure that participants correct or confirm any missing responses to questions on the page. The web application then transmits data entered by each participant through an encrypted network connection to a centralized database running on a secure network and infrastructure maintained by Emory University, ensuring secure electronic data movement.

Each participant is assigned a unique random number identifying him/her across study waves and REDCap projects. All identifiable data (names, contact info, etc.) and randomized ‘lower-intensity’ or ‘higher-intensity’ study arm assignment will be stored with the unique ID and accessible only to non-study staff. The Emory and Georgia State study teams will receive randomization data only after completing the main study analyses but will not have access to identifiers in the REDCap project. CCIHP and Emory staff will create and run applications for more refined range and consistency checks in the centralized database. Systematic data collection errors for each wave of data collection will be identified, resolved, and documented using the logging application in REDCap. For analyses done with external statistical software, de-identified data will be extracted and held on HIPAA-compliant, secure networks and computing workstations.

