#### Cost data (Aim 4).

The completed costing forms will be checked for consistency and missing information upon receipt. If any inconsistencies or missing information are found, the forms will be returned to CCIHP or the specific university via CCIHP for correction. Once the forms are verified as complete, they will be stored with a unique university ID and personnel ID in a folder accessible only to the health economist.

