## Statistical methods

### Statistical methods for primary and secondary outcomes {20a}

#### Qualitative data analysis (Aim 1).

Our analysis of qualitative data will be based on FRAME [36] to enable us to characterize and explain contextual facilitators and barriers to the implementation of GlobalConsent as well as planned and unplanned modifications to implementation strategies in the HIS and LIS groups. We will use rapid content analysis [80, 81] and a hybrid inductive-deductive approach [80, 81] to analyze the data. We will transfer all reflection notes, field diaries, and transcripts of KIIs and FGDs into matrices and use matrix analysis methods to examine core FRAME constructs of 1) engagement with the implementation training materials; 2) GlobalConsent delivery practices; 3) program modifications; 4) implementation strategies over time, including the nature of, timing, reasons for, and decision-makers involved in planned or unplanned implementation modifications; and 5) factors in the outer context or internal organizational context that may explain these modifications. Prior constructs and assumptions will be evaluated against the data, and new themes will be incorporated into the matrix coding scheme [82]. Matrices will systematically note the similarities, differences, and patterns in responses across participating universities and implementation-strategies groups, for a comparative synthesis of the findings [83]. Identifying these barriers, facilitators, and modifications, and their potential influence on implementation drivers and outcomes (Aim 2) and effectiveness (Aim 3) by implementation strategies group will provide insights about recommended adaptations to proposed implementation strategy bundles here as well as the time and skills needed to facilitate the implementation of GlobalConsent by operational partners at other universities.

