## Oversight and monitoring

### Composition of the coordinating centre and trial steering committee {5d}

The overall structure of the study team will include a central Steering Committee comprised of key personnel, each of whom is responsible for one or more specific aims and/or local imple-mentation of the project (**Figure 3**). The principal investigator (PI) at Emory University will chair the Steering Committee and will provide leadership for Specific Aims 1 and 3, related to implementation fidelity and effectiveness. The site-PIs at CCIHP and at Georgia State University will provide leadership for Specific Aim 2 on implementation drivers and outcomes. The health economist co-investigator at Georgia State University will provide leadership for Specific Aim 4 on cost-effectiveness and will provide overall statistical guidance to the study team. The site-PI and co-investigator at CCIHP will provide input on the research design and will lead external implementation support to participating universities in Vietnam. The IT company contracted in Vietnam will deliver the GlobalConsent program to participating students, will send reminders to complete each module, and will track adherence metrics at the student participant level. The Steering Committee will meet weekly to design, implement, and evaluate this initiative. A project coordinator / data analyst at Emory University will support the Steering Committee and will receive opportunities for professional development throughout the initiative. Pre-doctoral students at Emory University and Georgia State University will support all aspects of the research, from design to implementation and analysis and will receive capacity strengthening in research and opportunities for professional development.

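### The team-wide blinding claim cannot hold for the people who lead and statistically guide the effectiveness analysis

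*Protocol article*

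**What the plan says.** Section {17a} makes a claim about whole teams: "Study team members at Emory University and Georgia State University will be blinded to the assignments of universities until analyses are completed". The mechanism it names is a code: "by using a non-ordered numerical assignment to university and study arm in the REDCap database". Data management {19}, under quantitative data, adds access control. The stored arm assignment is open only to staff outside the study, and "The Emory and Georgia State study teams will receive randomization data only after completing the main study analyses". Section {17b} ties unblinding of study team members to the completion of the analyses for each aim.

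Other sections assign duties:

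- **Contracts, {11c}:** "Emory and CCIHP will establish deliverable-based contracts with each university clarifying the terms of reference (TOR) and payment schedule for mutually agreed implementation activities".
- **Aim 1 analysis, {20a}:** "Matrices will systematically note the similarities, differences, and patterns in responses across participating universities and implementation-strategies groups".
- **Cost forms, {19}:** once verified, "they will be stored with a unique university ID and personnel ID in a folder accessible only to the health economist".
- **Leadership, {5d}:** the Emory principal investigator "will provide leadership for Specific Aims 1 and 3, related to implementation fidelity and effectiveness". The Georgia State health economist "will provide leadership for Specific Aim 4 on cost-effectiveness and will provide overall statistical guidance to the study team".

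**The concern.** The two bundles consist of visibly different activities, so a record of what a university did is in effect a record of its arm. A code in the survey database hides the arm label in that database, but not in contracts, implementation transcripts or cost forms. If the people directing Aim 3 handle those records as part of their duties, the protocol claims for them a property that the design does not give.

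This matters because {20a} does not finally fix the student model. It selects the approach after inspecting pretreatment data and offers its equation as one possible form. It also gives two codings of the post-implementation term P. With a vector of period indicators, the HIS effect B5 is a set of period-specific contrasts. With a single before/after indicator plus a three-way interaction, B5 is the immediate shift and the slope change is estimated separately. The article expects results to favour HIS (Objectives {7}, Aim 3). Choices of this kind are safer when made without knowing which arm is which.

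**Working it through.** No sample size, power or alpha is involved, so the check sets the sections side by side.

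**1. Do activities reveal the arm?** Yes. According to {7}, {11a} and Tables 2 and 3, only HIS has faculty meetings, progress emails to leaders, an in-person student orientation, monthly learning sessions, two days of leadership training and six consultations with the training organisation (CCIHP). The orientation and leadership training are timed before implementation.

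**2. Who sees activities by university?**

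| Material | Holder | Link to a university | Duty in the effectiveness analysis |
|---|---|---|---|
| Contracts ({11c}) | Emory, with CCIHP | Direct: one per university | Principal investigator leads Aim 3 ({5d}) |
| Twelve CCIHP reflections on LIS and HIS ({12}), analysed as they accrue ({18a}) | Study team | Through content | Same person leads Aim 1 and Aim 3 |
| Aim 1 matrices ({20a}) | Aim 1 analysts | Compared by university and strategy group | Same person leads Aim 1 and Aim 3 |
| Cost forms per activity in Tables 2 and 3 ({12}, {18a}, {19}) | Georgia State health economist | University ID; total cost divided by that university's participants | Overall statistical guidance |

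**3. When?** Students are surveyed three times before and three times after delivery ({18a}), so wave 4 is the first post-implementation wave. Cost forms are collected monthly outside the 12-week delivery period and weekly within it, then sent to the economist. They cover the pre-implementation phase. Entries for HIS-only preparation therefore arise before wave 4.

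**4. Can knowledge of a named university's arm be carried to the coded student data?** This needs a link from university to code, which the article does not describe. Cluster size is one possible route. Table 1 gives 625, 600, 800, 449, 1,202 and 1,100 first-year men. At the planned 80% participation, university 4 has 449 × 0.80 = 359 participants and university 2, the next smallest, has 600 × 0.80 = 480. University 2 would have to fall below 359.2/600 = 59.9% to become the smaller.

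If participation lies anywhere from 70% to 90%, university 4 is always the smallest, because 449 × 0.90 = 404 is below 600 × 0.70 = 420. With participation drawn independently and uniformly from 60% to 100%, it was the smallest in 86% of 20,000 simulated draws. Linking one university whose arm is known decodes a two-valued arm variable for all six. This rests on 2021 enrolment estimates and assumed participation ranges. It shows that decoding is feasible, not that it will happen.

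**The case against.** Several points on the other side stand.

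- The blind does not rest on a code alone. Section {19} also restricts access to the arm assignment and delays its release.
- Transcripts and cost forms are de-identified, and the article does not say that the cost-form university ID matches the REDCap code. An analyst given only coded data could remain masked.
- Student outcomes are self-reported online, so assessment by unblinded staff is not in question.
- The article never presents blinding as the protection for model choice. That connection is an inference made here.
- Count distribution, lags and alternative trend forms are listed as sensitivity analyses under the male student analysis. A statistical analysis plan that is not shown may fix the primary model. Inspecting pretreatment data cannot reveal a post-implementation arm difference.
- A weekly Steering Committee meeting does not in itself disclose arms. The consultations are to be coded later, so early exposure through them is not documented.

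A reader might infer that the effectiveness analysis as a whole is unblinded, or that any report of blinded analysis would be false. The documents do not support that, because coded data and access control leave room for a masked analyst. What they contradict is the claim for the whole of both teams.

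Section {17b} does not remove the contradiction. Reflections are analysed and cost forms collected while the trial runs. If unblinding is read as staged by aim, finishing Aim 1 first would unblind the person who also leads Aim 3.

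**Conclusion.** The point holds for roles, not for the analysis as a whole. The declared blind cannot be maintained for the Emory principal investigator, the Aim 1 analysts or the Georgia State health economist. Contracts and cost forms cover all six universities, and arm-revealing content arises before wave 4. The contracts are the most direct link, assuming that those at Emory who set them up include, or report to, the person leading Aim 3. For the economist, the activity-level forms and the cost-per-participant calculation suffice.

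The consequence is limited to analytic choices: the form of the time-series model, the coding of P, and adjustments that the article says will be considered or made if necessary ({20a}, {20c}). Its effect on the estimate cannot be quantified from the documents. The text should be corrected, and the remedy is cheap.

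**What to change.** 1. In {17a} and {19}, name the roles that will be kept blind. Withdraw the claim for the principal investigator, Aim 1 analysts, health economist and anyone else with access to contracts, transcripts or cost forms.
2. Lock and date the primary time-series specification (trend form, coding of P, count distribution, adjustments) on arm-masked pre-implementation data before any wave-4 student data are opened. That includes data opened to prepare the monitoring board's descriptive tables. Report later departures as sensitivity analyses. If an analysis plan already does this, cite it and its date.
3. If blinded analysis is to be claimed, have the Aim 3 models run on coded arms by an existing team member without access to the revealing material. The Emory data analyst in {5d} is also the project coordinator supporting the Steering Committee, so that person qualifies only if those materials are closed to them. Recoding university IDs does not hide cluster sizes, so the separation has to rest on access.

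The cost is protocol wording, access permissions and a dated document. The drawbacks are less freedom to revise the model later and some separation of duties within a small team.
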